## Abstract

**Background:**

Many patients with diabetes mellitus (DM) require a combination of antidiabetic drugs with complementary mechanisms of action to lower their hemoglobin A_1c _levels to achieve therapeutic targets and reduce the risk of cardiovascular complications. Linagliptin is a novel member of the dipeptidyl peptidase-4 (DPP-4) inhibitor class of antidiabetic drugs. DPP-4 inhibitors increase incretin (glucagon-like peptide-1 and gastric inhibitory polypeptide) levels, inhibit glucagon release and, more importantly, increase insulin secretion and inhibit gastric emptying. Currently, phase III clinical studies with linagliptin are underway to evaluate its clinical efficacy and safety. Linagliptin is expected to be one of the most appropriate therapies for Japanese patients with DM, as deficient insulin secretion is a greater concern than insulin resistance in this population. The number of patients with DM in Japan is increasing and this trend is predicted to continue. Several antidiabetic drugs are currently marketed in Japan; however there is no information describing the effective dose of linagliptin for Japanese patients with DM.

**Methods:**

This prospective, randomized, double-blind study will compare linagliptin with placebo over a 12-week period. The study has also been designed to evaluate the safety and efficacy of linagliptin by comparing it with another antidiabetic, voglibose, over a 26-week treatment period. Four treatment groups have been established for these comparisons. A phase IIb/III combined study design has been utilized for this purpose and the approach for calculating sample size is described.

**Discussion:**

This is the first phase IIb/III study to examine the long-term safety and efficacy of linagliptin in diabetes patients in the Japanese population.

**Trial registration:**

Clinicaltrials.gov (NCT00654381).

## Background

Diabetes mellitus affects around 171 million people worldwide and this figure is expected to double by the year 2030. Type 2 diabetes mellitus (T2DM) accounts for between 90 and 95% of all cases of diabetes [1]. In Japan, the Ministry of Health, Labour and Welfare estimates that there are approximately 8.2 million people "strongly suspected of having diabetes" and there are about 10.5 million people "for whom the possibility of diabetes cannot be ruled out", suggesting that there could be as many as 18.7 million Japanese sufferers. In other words, one in four adults in Japan may have or may be in the process of developing diabetes [2]. Estimates suggest that 2.3 million Japanese people are currently receiving medical care for diabetes and reports place diabetes as the third most common cause of outpatient visits for Japanese men. The disease is also associated with significant co-morbidity and mortality, and ranks as the tenth most likely cause of death for Japanese men and the ninth for Japanese women [2]. Type 2 diabetes mellitus is a progressive disease and, once diagnosed, the treatment pathway involves an increasingly complex combination of treatments as the disease worsens. Despite the various treatments available, there is no cure and treatment regimens often become more complex as patients demonstrate progressive deterioration of glycemic control. Therefore, there is a recognized clinical need for safe and effective new treatments for T2DM. Dipeptidyl peptidase-4 (DPP-4) inhibitors are one such class of antidiabetic agents that have recently been introduced into the clinical armamentarium.

The purpose of a drug development program is to establish through clinical trials whether a drug displays acceptable levels of safety and tolerability, and to establish whether the drug's actions are both beneficial and clinically relevant. In T2DM, the gold standard measure of efficacy is the impact of the antidiabetic agent on levels of glycosylated haemoglobin (HbA_1c_). Although no superior marker to HbA_1c _has yet been proposed, its use raises a number of methodological and ethical challenges in terms of conducting clinical trials. In general, antidiabetic agents effect changes in HbA_1c _levels by only a few percent (typically 0.5-2%). In contrast, patients vary widely both in their individual HbA_1c _levels (7-14%) and in disease response to various treatments. The inherent variability of HbA_1c _levels within the diabetic population and the relatively small changes caused by treatment dictate that clinical studies attempting to establish the efficacy of a new drug for T2DM need to involve relatively large numbers of subjects to demonstrate any statistically significant results confirming efficacy. Where studies compare the efficacy of one drug relative to another, the number of subjects required needs to be greater still. Pressure to recruit sufficient numbers of patients in a timely fashion makes it impractical to conduct such studies using treatment-naïve patients alone, where recruitment ideally should occur at, or around the time of diagnosis. The design of studies must therefore consider using patients already receiving treatment for diabetes. This introduces a further complicating factor, as previous exposure to an antidiabetic treatment may affect patient response to new treatment.

Although HbA_1c _serves as an excellent indicator of change in the general level of individual glycemic control, it takes 2 - 3 months for any treatment-related changes to be fully represented within the HbA_1c _measurement for any patient. This influences the design and implementation of clinical trials of T2DM in several ways. First, studies must be conducted either in treatment-naïve patients, or in patients who have undergone a suitable treatment washout period so that HbA_1c _values are allowed to return to pre-treatment levels. Withholding therapy known to benefit a patient for up to 2 - 3 months could be considered unethical. Second, in light of the turnover of red blood cells, patients need to be exposed to an investigational drug for up to 12 weeks to demonstrate the full effect of the drug on HbA_1c _levels. Under these circumstances, if a study employs a standard placebo-controlled design, patients in the placebo group might go for up to 24 weeks without receiving diabetes treatment. Thus, the challenge in conducting clinical trials in T2DM is to design suitably powered efficacy studies that are both practicable and ethical. It is proving increasingly difficult to deliver such studies using traditional randomized, placebo-controlled designs. The employment of more complex trial designs that are appropriately powered may serve to address some of these challenges.

Dipeptidyl peptidase-4 (DPP-4) inhibitors are a new and promising class of agents for the treatment of T2DM. Linagliptin is a novel member of the DPP-4 inhibitor class that may offer added clinical benefits over similar agents. These include a long half-life consistent with once-daily dosing, non-renal excretion that will not require dose adjustment following loss of renal function and excellent safety and tolerability profiles [3-6]. As DPP-4 inhibitors increase insulin secretion, they are expected to become an important treatment for T2DM in Japanese patients, who tend to be leaner than patients in Western countries. Lean patients are more likely to be older at diagnosis, possess an immune component to their T2DM, and demonstrate certain pathophysiological characteristics, notably less insulin resistance and poorer insulin secretory capacity [7]. The present study proposes to investigate the effect of linagliptin on HbA_1c _levels in a Japanese population at two different doses (5 mg and 10 mg). It is possible that these patients will respond differently than Caucasian patients due to genetic differences. Differences in the pharmacokinetic and/or pharmacodynamic behaviour of drugs between Japanese subjects and subjects from other ethnic backgrounds have been observed, for example for the oral contraceptive Org 30659 [8] and the anti-cholesterol agent, rosuvastatin [9]. As a consequence, guidance from the Pharmaceutical and Medical Devices Agency (PMDA) in Japan recommends that the dose-response relationship for any new drug is confirmed in the Japanese population and that treatment is evaluated in 'adequate numbers of Japanese cases' [10].

The primary objectives of the proposed study are to compare the efficacy of linagliptin versus placebo in lowering HbA_1c _in a 12-week study conducted in Japanese patients with T2DM, and to examine the efficacy of linagliptin versus the antidiabetic agent voglibose. The study will also evaluate the long-term safety profile of linagliptin for up to 52 weeks. The study design, primary endpoints, patient inclusion/exclusion criteria and statistical methods used to calculate the study sample size are described.

## Methods/Design

### Study Setting

This is a randomized, double-blind study with both a placebo- and an active-controlled parallel group. It is conducted in 47 centers in Japan. To be eligible for study enrollment, male or female subjects are required to be Japanese patients aged 20-80 years with T2DM (baseline HbA_1c _levels of 7.0-10.0%). Patients taking oral anti-hyperglycemic drugs at screening are eligible to participate if they have a mean HbA_1c _value of > 7 - < 9% during the washout period. Other inclusion criteria include a stable HbA_1c _value (less than 10% variation during the last 2 weeks of the 4-week washout period) and a body mass index less than 40 kg/m^2 ^at randomization. Patients are excluded from the study if they violate these inclusion criteria or if they meet the exclusion criteria specified in the protocol.

All patients must give written consent to participate in the study, which has been approved by an Institutional Review Board at each center. This study is registered with the US National Institutes of Health website: ClinicalTrials.gov (NCT00654381).

### Study Stages

This study includes three different stages, each with specific objectives, and will utilize four treatment arms (A-D) (see Figure 1). The objective of Stage 1 is to compare changes in HbA_1c _levels in patients receiving linagliptin with those receiving placebo at 12 weeks. The objective of Stage 2 is to compare changes in HbA_1c _levels in patients receiving linagliptin with those receiving voglibose after 26 weeks of treatment. The objective of Stage 3 is to determine the long-term safety and tolerability of linagliptin.

**Figure 1 F1:**
[figure not shown]
**Study Design**.

Initially, patients will undergo a washout period where they receive placebo for 4 weeks after providing informed consent. Following the washout period, eligible patients will be randomized to one of four treatment arms (placebo [A]; linagliptin 5 mg [B]; linagliptin 10 mg [C]; or voglibose 0.6 mg [D]). Patients randomized to Group A will receive a placebo for 12 weeks after which they will receive linagliptin for 40 weeks; patients in the Group B (linagliptin 5 mg) and Group C (linagliptin 10 mg) treatment arms will receive the study drug for up to 52 weeks. Patients randomized to Group D (voglibose 0.6 mg) will receive the treatment for 26 weeks after which they will be switched to linagliptin for 26 weeks (Figure 1). The treatment change to linagliptin in Groups A and D involves an additional patient randomization to either 5 mg or 10 mg, from which data on the long-term safety and tolerability of linagliptin will be collected. The doses of linagliptin used in this study are based on previous reports of DPP-4 activity in Japanese T2DM patients [11].

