### Study Randomization

Four treatment arms are used to investigate the effective dose and safety profile of linagliptin in the study population. Randomization will be based on the Zelen rule [13] and follow a predefined allocation ratio of 2:2:2:1 (linagliptin 5 mg: linagliptin 10 mg: voglibose: placebo). Allocation to treatment groups is balanced for the potentially confounding effects of patient background and baseline characteristics, HbA_1c _(stratified into two categories; < 8.5% and ≥ 8.5%), the number of pre-study use of antidiabetic drugs, gender and study site.

Treatment allocation is conducted by a sponsor-independent contractor. Following informed consent, the investigator completes a registration form that is sent to the allocation center. The registration form includes data on the subjects' inclusion and exclusion criteria. After receiving the registration form, the allocation center sends a registration report to the investigator. The investigator confirms that the patient satisfies the study criteria and sends a second registration form to the allocation center once the 4-week washout period is completed. The allocation center randomizes the patient according to the pre-defined criteria above and this information is provided to the investigator. Randomization is done once at the enrollment of study. At the randomization after the enrollment, patients are assigned, to 6 groups: placebo - linagliptin 5 mg, placebo - linagliptin 10 mg, linagliptin 5 mg, linagliptin 10 mg, voglibose - linagliptin 5 mg, and voglibose - linagliptin 10 mg. Therefore all patients ultimately take either linagliptin 5 mg or 10 mg, unless they withdraw or drop out the study.

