#### Analysis for the primary endpoint

Baseline glycosylated hemoglobin levels and the number of antidiabetic drugs used before study enrollment are included in the model as covariates.

Changes in HbA_1c _level from baseline to 12 weeks of linagliptin treatment are analyzed in accordance with the model below, in order to compare with placebo in the double-blind treatment phase:

Where:

*y*_*ijk *_: change in HbA_1c _at 12 weeks from baseline

*BHbA1c*_*i *_: HbA_1c _of i-th patient at baseline (i = 1, 2,..., n)

*Dose*_*j *_: j-th dose group (j = 0: placebo, 1: 5 mg, 2: 10 mg)

*Diabtreat*_*k *_: number of previously used antidiabetic drugs (k = 0: no treatment, 1: one antidiabetic drug, 2: two antidiabetic drugs)

Comparisons conducted at 12 weeks are between linagliptin and placebo. Patients who received placebo for 12 weeks and are then randomized to receive either linagliptin 5 mg or 10 mg are excluded from this analysis. Values of HbA_1c _following treatment with linagliptin are to be compared with those for voglibose after 26 weeks if linagliptin treatment fails to achieve a statistically significant difference in HbA_1c _levels relative to placebo (primary comparison dose at 12 weeks). The dosing schedule for linagliptin increases from 5 mg to 10 mg during study if linagliptin 5 mg fails to demonstrate superiority to placebo at 12 weeks. In addition, the study stops if neither of the linagliptin arms shows statistically significant differences from placebo in HbA_1c _levels at 12 weeks.

The model for HbA_1c _at 26 weeks is:

Where:

*y*_*ijk *_: Change in HbA_1c _at 26 weeks from baseline

*HbA1c*_*i *_: HbA_1c _of i-th patient at baseline (i = 1, 2,..., m)

*Drug*_*j*_: j-th treatment group (j = 1:5 mg, 2:10 mg, 3:voglibose)

*Diabtreat*_*k *_: number of previously used antidiabetic drugs (k = 0:no treatment, 1:one antidiabetic drug, 2:two antidiabetic drugs)

Comparisons for HbA_1c _between groups are performed weekly by the closed testing procedure [15]. No formal analysis will be performed for safety and tolerability data collected during the three stages of the study. Data will be summarized in terms of treatment received.

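### The number of randomizations is stated two ways, and the week-12 exclusion sentence that carries one of them would, read literally, remove the placebo comparator

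*Protocol article*

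**What the plan says.** Study Stages (text under Figure 1) describes two steps. After washout, "eligible patients will be randomized to one of four treatment arms". Later, the move to linagliptin in the placebo and voglibose groups "involves an additional patient randomization to either 5 mg or 10 mg".

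Study Randomization describes one step: "Randomization is done once at the enrollment of study". It continues: "At the randomization after the enrollment, patients are assigned, to 6 groups". The six are placebo then 5 mg, placebo then 10 mg, linagliptin 5 mg, linagliptin 10 mg, voglibose then 5 mg, and voglibose then 10 mg. The stated allocation ratio is 2:2:2:1 for linagliptin 5 mg, linagliptin 10 mg, voglibose and placebo. No ratio is given within placebo or within voglibose.

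Analysis for the primary endpoint, on the week-12 comparison with placebo, states: "Patients who received placebo for 12 weeks and are then randomized to receive either linagliptin 5 mg or 10 mg are excluded". The model in the same section keeps placebo as a level: "j-th dose group (j = 0: placebo, 1: 5 mg, 2: 10 mg".

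Statistical analysis commits to intention-to-treat with a full analysis set. Sample size requires at least 52 placebo patients and 104 per linagliptin group, with targets of 63 and 126 and a total of 441.

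**The concern.** A second randomization at the switch and a single randomization at enrollment are different procedures, and the article states both. This is not detail left to the full protocol.

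On its own the mismatch is a matter of description. It concerns how the later linagliptin dose is allocated for the placebo and voglibose groups, which are 63 + 126 = 189 of the 441 planned patients (43%). That is a headcount, not a bias or a loss of power.

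The stakes come from the exclusion sentence. It borrows the two-step wording, stands next to the statement that week 12 compares linagliptin with placebo, and excludes patients rather than data collected after the switch. Every placebo patient is meant to move to linagliptin after week 12. A programmer who applied the sentence as written could therefore lose the reference group of a primary comparison.

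**Working it through.** **1. The plan's own figure.** Inputs from Sample size: difference 0.5, SD 0.9, one-sided 2.5%, power 90%, placebo to linagliptin 1:2.

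n(placebo) = (1 + 1/2) × (0.9/0.5)² × (1.960 + 1.282)² ≈ 1.5 × 3.24 × 10.51 ≈ 51.1, rounded up to 52, with 104 on linagliptin.

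The noncentral t distribution, with noncentrality 0.5 / (0.9 × √(1/52 + 1/104)) = 3.27, gives power 90.2%. The stated 52 and 104 are reproduced.

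For week 26 (difference 0.45, SD 1.0, 1:1), the t-based size is 105 per group with power 90.1%, also as stated.

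Dropout: 52/0.85 gives 62, 104/0.85 gives 123 and 105/0.85 gives 124, against targets of 63 and 126. These agree within rounding that keeps 1:2. The total is 63 + 3 × 126 = 441.

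None of these figures depends on when the 5 mg or 10 mg sub-allocation is made. In both descriptions all placebo patients receive placebo to week 12 and all voglibose patients receive voglibose to week 26.

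**2. The exclusion sentence under each description.**

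| Randomization | Reading of the sentence | Placebo patients left at week 12 |
|---|---|---|
| Second one at the switch (Study Stages) | literal | only those who left before the switch |
| Once, to six sequences (Study Randomization) | literal: nobody is randomized later | all; the sentence is empty |
| Once, to six sequences | taken as assigned to switch | none; both placebo sequences switch |

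**3. Size of the first row.** The article gives 15% dropout over 52 weeks but not its timing, so the timing is an assumption.

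- All dropout before week 12: 63 × 0.15 = 9.45, at most about 10 patients.
- Dropout spread evenly over 52 weeks: 63 × 0.15 × 12/52 = 2.2, about 2 patients.

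Take 126 × 0.85 ≈ 107 patients on one linagliptin dose and the plan's effect and SD:

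- 10 against 107: noncentrality 0.5 / (0.9 × √(1/10 + 1/107)) = 1.68, power about 38%.
- 2 against 107: noncentrality 0.5 / (0.9 × √(1/2 + 1/107)) = 0.78, power about 12%.

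These powers only illustrate scale. A placebo group made up solely of early dropouts is no longer a randomized comparator, whatever its size.

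**4. Against the rest of the plan.** The first and third rows both conflict with the placebo level of the week-12 model, with the 52 placebo patients required, and with intention-to-treat. Only the row in which the sentence does nothing is consistent with them.

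**The case against.** The strongest reply is that no one intends to discard the placebo arm. The model, the stated comparison and the sample size all need it. A sensible reading is that former placebo patients are simply not counted with the linagliptin groups after they switch, and that gives the same week-12 set under either procedure. As a guess at intent this is persuasive. It is not what the sentence says, since the sentence excludes patients from the analysis.

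A second reply is that Study Randomization is the dedicated section and states the procedure clearly, so the Study Stages text may be a loose account of the same pre-assigned sequences. That is possible, and it is why the former should be treated as the explicit text. The primary analysis section repeats the two-step wording for placebo patients, however, so it is not an isolated slip. It does not mention the voglibose group; for that group the second randomization rests on Study Stages alone.

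Three stronger readings are tempting, and the document does not support them:

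- **That settling the number of randomizations settles the week-12 population.** It does not. The exclusion sentence is defective or empty under either procedure and needs its own correction.
- **That the placebo arm has either about 54 patients (63 × 0.85 = 53.6) or none, depending on the procedure.** The 15% applies to 52 weeks, a full analysis set could hold up to 63, and the literal rule under a second randomization leaves early dropouts rather than nobody.
- **That the Stage 3 dose comparison is compromised.** The article plans no formal analysis of safety and tolerability and summarizes these data by treatment received, so the effect there is on description only.

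**Conclusion.** The point holds as an internal contradiction with one consequential sentence. The two accounts of the randomization cannot both be right. By itself the disagreement leaves the week-12 and week-26 comparisons and the sample size untouched.

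The exclusion sentence is wrong as written. If it is applied literally with a second randomization, about 2 to 10 of 63 placebo patients remain, where 52 are required. If it is read as covering everyone assigned to switch, none remain. The range of 2 to 10 rests on the assumed timing of a 15% dropout rate that the article gives only for 52 weeks. It shows what the text would do, not what the sponsor is likely to do. Correction before analysis is warranted and proportionate.

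**What to change.** 1. In Study Stages, remove the reference to an additional randomization and describe one randomization at enrollment to six sequences, in line with Study Randomization.
2. State the split within placebo and within voglibose. If it is 1:1, which is an assumption and is not in the article, 2:2:2:1 becomes 4:4:2:2:1:1 (5 mg, 10 mg, voglibose then 5 mg, voglibose then 10 mg, placebo then 5 mg, placebo then 10 mg). A placebo target of 63 cannot be halved exactly.
3. In Analysis for the primary endpoint, delete the exclusion sentence or rewrite it so that only HbA1c data collected after the switch to linagliptin are left out. This is needed whichever randomization procedure is kept. Adding a pooling statement beside the existing sentence would create a new contradiction.
4. State that both placebo sequences are pooled as the placebo arm at week 12 and both voglibose sequences as the voglibose arm at week 26.

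The cost is wording only. With no placebo patient excluded at week 12, the 52:104 calculation keeps its 90% power and the total of 441 stands.

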### Study Endpoints

The proposed comparison of efficacy between linagliptin (5 and 10 mg) and both placebo and voglibose is based on changes in HbA_1c _levels from baseline at 12 and 26 weeks, respectively. The primary comparison between linagliptin 10 mg and placebo is planned at 12 weeks, and the comparison between linagliptin 10 mg and voglibose 0.6 mg is planned at 26 weeks. To investigate dose-response relationships, a subsequent comparison is made at those time points between linagliptin 5 mg and placebo (12 weeks) and voglibose 0.6 mg (26 weeks).

Other parameters of interest measured will include inhibition of plasma DPP-4 activity, the proinsulin/insulin ratio, the homeostasis model assessment (HOMA) indices for insulin resistance and insulin secretion, body weight, waist circumference and plasma concentrations of linagliptin. Adverse event, safety, laboratory and hematology data will be collected during the study and will form part of the secondary endpoint data for determining the long-term safety profile of linagliptin.

Patient reported outcomes will be assessed using the Diabetes Treatment Satisfaction Questionnaire (DTSQ) modified by Ishii [12], consisting of 6 items assessing treatment satisfaction and 2 items assessing the perceived frequencies of hyperglycaemia and hypoglycaemia.

